**Figure 1 figure1:**
[figure not shown]
Overview of study design. ELISA: enzyme-linked immunosorbent assay; PCR: polymerase chain reaction.

**Table 1 table1:** Nutrient composition of test crackers.

Nutrient composition			80-g portion of crackers		
			Refined soft white wheat flour crackers	Whole-grain soft white wheat flour crackers	Whole-grain soft red wheat flour crackers
Calories (kcal)			313	298	306
**Fat (g)**			6.44	7.16	8.00
	Saturated fat		1.68	1.82	2.08
	MUFA^a^		1.26	1.41	1.59
	PUFA^b^		3.16	3.54	3.92
	Trans fat		0.058	0.071	0.082
Protein (g)			7.15	9.10	9.35
**Carbohydrates (g)**					
	**Total dietary fiber**		3.99	10.72	10.72
		Insoluble fiber	1.54	7.54	7.35
		Soluble fiber	2.45	3.18	3.37
Sodium (mg)			439	452	454

^a^MUFA: monounsaturated fatty acids.

^b^PUFA: polyunsaturated fatty acids.

### Setting and Participant Recruitment

This study will be conducted during the summer in East Lansing, Michigan, on the campus of Michigan State University and will enroll 30 adults. Subjects will be recruited via flyers hung in buildings around the Michigan State University campus as well as through the Michigan State University–paid research pool [31]. To be included in the study, participants must be aged between 18 and 55 years as the gut microbiota matures by adulthood and remains stable throughout [1]. Participants must also have bowel movements at least once every 3 days, be willing to eat wheat crackers, and be available for weekly lab visits. Participants will be excluded if they take any nonsteroidal anti-inflammatory drugs, antacids, proton pump inhibitors, nutritional supplements, or multivitamins daily; have taken any antibiotics in the 2 weeks before the study; have gastrointestinal issues or diabetes; are pregnant; are following any special diet; or have food allergies. Participants will be provided with a US $50 cash incentive upon completion of the dietary intervention. All participants will provide written informed consent.

### Dietary Intervention

The dietary intervention will consist of a 4-week period of wheat consumption in the form of wheat crackers. Each week, participants will be given 7 bags of crackers (1 bag for each day of the week), containing approximately 80 g of baked crackers per bag, to be eaten throughout the following week. Each 80 g cracker allotment will provide approximately 10.7 g of total dietary fiber for crackers made from either whole-grain soft white flour or whole-grain soft red flour. The nutrients and calories of the 80 g cracker allotment consumed per day are listed in Table 1.

Crackers for each treatment week will be made in bulk to yield 260 daily portions (7 portions per participant plus extra), with approximately 80 g of baked crackers per daily portion per person. The cracker was formulated as 100 g flour (approximately 13% moisture), 1.5 g of iodized salt, 2 g of sugar, 6 g of vegetable shortening, and 49 to 50 g of tap water. The proportions of flour, salt, and sugar, according to the formulation stated above, will be added into the bowl of a Hobart mixer (model A-200) and whisked to combine the dry ingredients. Fat will be added to the dry ingredients and mixed until the fat particles are reduced in size to approximately 1 to 2 mm. Water will then be added and mixed until a firm dough forms. The amount of water (approximately 48 g) will need to be adjusted to ensure that all flour is fully hydrated. The dough will then be portioned by dividing it into 127 g aliquots based on the expected yield of 80 g of baked crackers per 127 g of dough (determined in preliminary testing). Each 127 g portion will be flattened between two pieces of parchment paper using a dough sheeter set to 3/32 inch. The top sheet of the parchment paper will be removed, and the dough will be cut into approximately 1- to 2-cm-wide strips. Crackers from each portion of dough will be baked in a carousel oven for approximately 11 to 12 minutes at 400 °F until browned. Crackers will be cooled on a rack on the workbench before being placed into individual resealable portion bags labeled *day 1* to *day 7*; then, 7 bags will be placed in one larger bag to be distributed to each participant.

As this study involves adding approximately 300 calories of carbohydrate-containing food to the daily diet, participants will receive flyers (Figure 2) informing them how to incorporate the crackers into their diets by replacing everyday dietary items such as cereals and bread with the test crackers. This will prevent or minimize participants’ weight gain.

**Figure 2 figure2:**
[figure not shown]
Flyer to be distributed to participants providing calories in common serving sizes of typical carbohydrate-containing foods.

### Outcomes

#### Overview

At the conclusion of each week, stool samples will be collected for analysis. The primary outcome measure will be the alpha diversity of the gut microbiota. This will be measured using the sequencing data obtained from the participants’ stool samples after DNA extraction and polymerase chain reaction (PCR) amplification of the V4 region of the 16S rRNA gene. The secondary outcome measure will be biomarkers of gastrointestinal inflammation, as measured by protein concentrations of calprotectin and lipocalin-2 in protein extracts of the stool samples. Furthermore, the microbiota beta diversity, abundance of *Bifidobacterium* and *Lactobacillus,* and butyrate production capacity of the gut microbiota will be assessed after each week of treatment. The abundance of *Bifidobacterium* and *Lactobacillus* will be determined from the sequencing results. The butyrate production capacity will be determined by quantitative real-time PCR assays targeting the bacterial butyrate kinase and butyrate transferase genes [32].

#### Other Measurements

Background characteristics of the study participants will be recorded during recruitment when each participant will complete a short questionnaire. In addition, current weight, health status, 24-hour dietary intake, and water source will be collected each week along with a fiber intake questionnaire (described below) recording the amount of fiber-containing foods consumed throughout the week. A 24-hour recall will be implemented as this has been previously reported to supply sufficient information to interpret microbiota data from participants’ fecal samples [33]. Participants will self-report their 24-hour dietary intake by free response to the question “What did you eat and drink in the past day? (Please give as much detail as possible, including the estimated amounts).”

### Data Analysis

#### Diet Analyses

##### Overview

Individual diet diversity scores will be calculated for each participant at each time point. The use of the diet diversity score provides a more general measure of the variety of dietary intake than specific food consumption data. This scoring system counts the number of food groups consumed by an individual. Data will be supplied based on the 24-hour intake data provided in response to this prompt, “What did you eat and drink in the past day? (Please give as much detail as possible, including the estimated amounts.)” as well as their answers to a checklist of 34 food and supplement items where participants are prompted to “Place an 'x' in the box next to anything that you ate in the past 24 hours.” The food checklist was designed to capture the intake of the foods listed in the diet diversity scoring tool document of the Food and Agriculture Organization of the United Nations [34]. Dietary diversity score will be assessed as described by the Food and Agriculture Organization of the United Nations [34].

##### Fiber Intake Analysis

The PhenX fiber intake protocol will be used to assess additional dietary fiber intake [35]. Each week, participants will receive a screener (PhenX protocol 50601) asking them to report how often they consumed different types of fiber-containing foods (ie, cereal, vegetables, and beans). Participants will record how often they consumed a portion of food—never, less than once a day, once a day, twice a day, three times a day, four times a day, or five or more times per day. A score will be assigned to each participant at each time point using the scoring methods provided by the PhenX protocol. This score will be used to account for the fiber in the diet that is not from the test crackers.

#### Microbiota Analyses

Stool samples will be extracted, prepared for sequencing of the 16S rRNA gene, and sequenced as described in references [36-38].

#### Butyrate Gene Analyses

Quantitative real-time PCR will be performed on the genomic DNA from each sample to determine the levels of butyryl-CoA: acetate CoA-transferase (*but*) and butyrate kinase (*buk*). Primer sets, But_RosEub, But_G.prausn, and Buk, previously designed by Vital et al [32], will be used. All genomic DNA samples will be diluted to 2.5 to 5 ng/μL. In a 96-well plate, genomic standards at concentrations of 10^2^ to 10^7^ will be used to create a standard curve. All wells will be filled with 7.5 μL SYBR Green, 3.5 μL ddH_2_O, 1 μL F primer, 1 μL R Primer, and 2 μL template. The thermocycling program to be performed is as follows: 2 minutes at 50°C, 10 minutes at 95°C, 45 seconds at 95°C, 45 seconds at annealing temperature for the specific primer, and 45 seconds at 72°C for 40 cycles. A one-way repeated-measures analysis of variance (ANOVA) will be performed on each set of data to compare the relative abundance and presence of the following butyrate synthesizers: *Faecalibacterium prausnitzii*, *Eubacteria *spp., *Roseburia *spp., and *Clostridium acetobutylicum*.

#### Intestinal Inflammatory Protein Analyses

Proteins will be extracted from the stool samples. The extraction buffers for lipocalin (catalog number 30757) and calprotectin (catalog number 30473) will be purchased from Epitope Diagnostics, Inc. First, the fecal samples will be aliquoted and stored at −80°C until protein extractions are performed. Then, approximately 100 mg of fecal material will be aliquoted into a conical tube, and the exact weight of the sample will be recorded. Each sample will be extracted separately with each of the two extraction buffers. Using a serological pipette, 4 mL of extraction buffer per 100 mg of stool will be aliquoted into a conical tube for each sample. Each tube will be gently vortexed and incubated at room temperature on an orbital shaker for 30 minutes. The protein extracts will then be aliquoted into microfuge tubes and stored at −80°C until ELISAs (enzyme-linked immunosorbent assays) are performed. The ELISA kits will be purchased from R&D Systems (a Bio-Techne brand) for human calprotectin (S100A8/S100A9; DS8900) and human lipocalin-2 (neutrophil gelatinase-associated lipocalin; DLCN20). Fecal extracts will be diluted at 1:25 or 1:100 in sample diluent for calprotectin assays and 1:20 or 1:100 in sample diluent for neutrophil gelatinase-associated lipocalin assays.

### Statistical Analyses

Statistical analysis of differences between pre- and posttests will be assessed using ANOVA or Friedman Wilcoxon rank-sum tests [39]. Multivariate statistics will be performed using R (R Foundation for Statistical Computing), a free statistical software program. To compare the alpha diversity of the microbial communities, Chao1 (a measure of richness), inverse Simpson (a measure of richness and evenness, with emphasis on evenness), and Shannon diversity (a measure of richness and evenness, with emphasis on richness) will be calculated in R using the vegan package [40]. ANOVA and Wilcoxon signed-rank test or Friedman test with post hoc comparisons will be used to compare alpha diversity across treatment categories after intervention [41]. For beta diversity, Bray-Curtis and Sorenson distances will be used with principal coordinates analysis ordination to produce plots of the distances between samples. Differences in beta diversity between time points will be determined using permutational multivariate ANOVA (PERMANOVA) via the adonis function in the vegan package, and differences in group dispersion will be determined using PERMDISP [40]. PERMANOVA may also be used to determine the relationship between the distance metrics and wheat variety, as well as other variables. Metastats (a function of the mothur software package) will be performed on the subsampled abundance data to test for significant differences in operational taxonomic unit abundance between groups [42]. Changes in taxa (both genus and phylum level) >1% average relative abundance will be determined across time points using the Friedman test with post hoc comparisons. Where appropriate, the negative binomial and zero-inflated mixed models in the R package will be used to test for differences in taxa abundance over time [43].

Enterotypes will be manually assigned based on clustering within quadrants in a Bray-Curtis principal coordinates analysis plot overlaid with the most abundant taxa driving community differences, as in Wu et al [4], using the envfit function in the vegan package. Significant differences between enterotypes will be determined using ANOVA for parametric data and the Kruskal-Wallis test for nonparametric data. Differences between time points within each enterotype will be determined using the Friedman test with post hoc comparisons.

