## Methods

### Design

This wheat intervention study will characterize the variable response of gut bacteria to supplementation in adult humans. Treatments will include (1) refined soft white wheat flour, (2) bran-containing whole-wheat flour of Michigan soft white wheat, or (3) bran-containing whole-wheat flour of Michigan soft red wheat. All 3 flour samples will be provided by King Milling Company (Lowell, Michigan). Each of the two whole-wheat interventions will be administered over a 1-week period, with a baseline week (refined soft white wheat flour) before the intervention begins and a washout week (refined soft white wheat flour) between the two test periods (Figure 1). Wheat flour will be administered to participants in the form of wheat crackers. The nutrient composition of the wheat crackers is provided (Table 1)**.** During each of the two test periods, 80 g of crackers made from whole-grain soft white wheat flour or whole-grain soft red wheat flour will provide each participant with approximately 10.7 g of total dietary fiber per day (Table 1). At the end of each 1-week treatment period, a stool sample as well as answers to a health and fiber intake questionnaire, will be collected from each participant. A total of 4 stool samples will be collected from each participant over the course of the study. Microbiome samples will be aliquoted and stored at −80°C until analysis.

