### Strengths and Weaknesses

An important strength of this study is the composition of the crackers. The aim of the study is to test the effect of specific types of wheat; thus, it is important to note that we have created a cracker formulation that is composed almost entirely of the wheat of interest with few additional ingredients. The simple recipe we have developed for the crackers will improve confidence that the differences observed in the microbial community and inflammatory biomarkers are owing to the consumption of the wheat in the study crackers rather than a different ingredient in the treatment food. The quick turnaround from the cracker intake to sample collection also helps strengthen the study. Stool samples will be collected on the final day of each week's cracker intake, ensuring that little time has elapsed between the last cracker intake and stool sample collection. This is important for microbiota analyses as the temporal intake of food is tightly associated with microbial composition [51]. In addition, we will allow sufficient time to pass between each intervention through the use of a washout period. Johnson et al [33] described a minimum 3- to 5-day period between crossing-over diets to allow the microbiome to return to baseline. The crossover design of this study will allow us to perform within-person comparisons, placing less emphasis on interindividual differences in the gut microbiome [33].

A potential limitation of our study may be participant retention. Participants will be expected to consume approximately 80 g of crackers every day for 4 weeks, so it is important that they enjoy the taste of the crackers to ensure their compliance and continuance in the study. However, the study participants may tire of the taste of the crackers. A high dropout rate could hinder our ability to detect statistically significant differences.

Whole grains alleviate dysbiosis in the gut microbiota; however, little is known about the impact of different wheat types on this phenomenon [12,18,20]. A 4-week wheat intervention to investigate the effect of different types of Michigan-grown wheat on the gut microbiota is described in this protocol. The results of this study will improve our understanding of the unique effects of different types of wheat on gut microbiota and on the inflammatory state of the human gastrointestinal tract.

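### Paired, unpaired and unspecified tests are mixed for repeated samples from the same 30 people, and the inflammation biomarkers have no clearly paired method

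*Protocol article*

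**What the plan says.** The article "will enroll 30 adults" (Setting and Participant Recruitment). Under Design, "A total of 4 stool samples will be collected from each participant over the course of the study". Strengths and Weaknesses draws the statistical consequence: "The crossover design of this study will allow us to perform within-person comparisons, placing less emphasis on interindividual differences in the gut microbiome".

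Statistical Analyses opens with a general rule: "Statistical analysis of differences between pre- and posttests will be assessed using ANOVA or Friedman Wilcoxon rank-sum tests". Method-specific sentences follow. For beta diversity: "Differences in beta diversity between time points will be determined using permutational multivariate ANOVA (PERMANOVA) via the adonis function in the vegan package". For operational taxonomic units: "Metastats (a function of the mothur software package) will be performed on the subsampled abundance data", with the purpose given as finding differences between groups.

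Other sentences name paired methods. Alpha diversity gets ANOVA and the signed-rank test, or Friedman; this matters because "The primary outcome measure will be the alpha diversity of the gut microbiota" (Outcomes, Overview). Genus and phylum changes, and time points within an enterotype, get Friedman. Taxa over time may get negative binomial or zero-inflated mixed models. Butyrate Gene Analyses specifies a one-way repeated-measures ANOVA.

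**The concern.** Every comparison of one week with another sets a person against himself or herself. A test for independent groups leaves the variation between people in the error term, which is the variation the crossover argument says is set aside. The general rule names such a test, while the alpha-diversity sentence in the same section names its paired counterpart, so the section disagrees with itself about the same kind of data.

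Two places are most exposed. The first is intestinal inflammation, the secondary outcome and the subject of a stated hypothesis (red whole wheat against refined white). The second is community composition, where the hypothesis is that white and red whole wheat favour different microbes. A real effect could be reported as no difference. Leaving paired and unpaired tests both open would also let the choice be made after the results are seen.

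**Working it through.** **1. What each outcome is given.**

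| Comparison | Method named | Paired? |
|---|---|---|
| Pre/post, general rule | ANOVA, type unstated; Friedman joined to rank-sum | Not identifiable |
| Alpha diversity (primary) | ANOVA, type unstated, and signed-rank; or Friedman | Paired options named |
| Beta diversity between time points | adonis, PERMDISP | Participant not mentioned |
| Operational taxonomic units | Metastats, between groups | Unpaired as described |
| Genus and phylum changes | Friedman | Yes |
| Taxa over time | Mixed models | Can carry a participant effect |
| Butyrate genes | Repeated-measures ANOVA | Yes |
| Calprotectin, lipocalin-2 | General rule; abstract's ANOVA or linear regression | None clearly paired |
| Responders vs nonresponders | ANOVA or rank-sum | Unpaired, correctly: different people |

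**2. What is at stake.** The article gives no effect size, SD, within-person correlation or power, so there is no figure to reproduce. Assumptions: n = 30 with complete data, two-sided alpha 0.05, a shift of 0.5 SD, and within-person correlation ρ from 0.3 to 0.7.

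- Standard error assumed by an unpaired test: √(2/n) = √(2/30) = 0.258.
- True standard error of the difference: √(2(1−ρ)/n). At ρ = 0.5 this is √(1/30) = 0.183.
- Paired power at ρ = 0.5 (normal approximation): Φ(0.5/0.183 − 1.96) = Φ(0.78) = 0.78.
- Unpaired power at ρ = 0.5: 1 − Φ((1.96 × 0.258 − 0.5)/0.183) = 0.49.
- Unpaired true alpha at ρ = 0.5: 2[1 − Φ(1.96 × 0.258/0.183)] = 0.006.

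Simulation with the named tests, 4,000 runs per setting (the ANOVA columns use four weeks with both whole-wheat weeks shifted):

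| ρ | Rank-sum power | Signed-rank power | Ordinary ANOVA power | Repeated-measures ANOVA power | Rank-sum true alpha |
|---|---|---|---|---|---|
| 0.3 | 0.45 | 0.60 | 0.59 | 0.76 | 0.026 |
| 0.5 | 0.43 | 0.73 | 0.55 | 0.90 | 0.008 |
| 0.7 | 0.44 | 0.92 | 0.51 | 0.99 | about 0 |

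Rank-sum power is flat in ρ only because the unpaired critical difference, 1.96 × 0.258 = 0.506 SD, almost equals the assumed shift. For a shift of 0.3 SD it falls as ρ rises: 17%, 11% and 7%, against 26%, 34% and 52% for signed-rank.

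**3. PERMANOVA.** Two time points, Euclidean distance, 10 dimensions, 0.25 SD shift in each, 300 runs of 199 permutations. Free permutation gave power 0.18 against 0.86 within participant at ρ = 0.5, and 0.01 against 1.00 at ρ = 0.8. With no effect, the rejection rates were 0.00 and 0.05.

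**4. Which model can be fitted.** Refined crackers fill weeks A and C, and whole wheat weeks B and D, for everyone. If week is categorical, the white and red indicators sum to the week B and week D indicators. The six columns (intercept, three weeks, white, red) then have rank 5 if the order of the two whole wheats varies between people and rank 4 if it is fixed. Either way, refined versus whole wheat, the primary aim, cannot be estimated alongside a categorical week term.

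**The case against.** The strongest reply is that the plan is largely paired already. The primary outcome has signed-rank or Friedman, taxa have Friedman or mixed models, and the butyrate genes have repeated-measures ANOVA. A reader might infer from the general rule that the within-person comparison is thrown away throughout, or that power for alpha diversity drops to the rank-sum figures. The documents do not support either inference, because the alpha-diversity sentence does not name rank-sum.

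Three further points stand in part:

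- That ANOVA means the ordinary kind is an inference. The type is unstated, and repeated-measures ANOVA is in use elsewhere.
- The absence of blocking in adonis is silence, and function arguments are detail a condensed article may leave to the full plan. It cannot be asserted that labels will be shuffled across people.
- Metastats may be meant for true groups such as enterotypes or responders. Use on weeks is the likelier reading, since the neighbouring sentences concern time points, but it is not certain.

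None of this answers the general rule itself, which names a test for independent groups for pre/post data. Nor does it supply a paired method for calprotectin and lipocalin-2.

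**Conclusion.** The point holds in limited form. The general pre/post rule is wrongly worded, the secondary outcome rests on it with no clearly paired method, and the handling of participant is unstated for adonis and for any use of Metastats across weeks. This sits badly with the article's own within-person rationale.

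A reader might fear spurious findings. The direction is the opposite: treating positively correlated samples as independent makes week comparisons too conservative. At an assumed 0.5 SD shift and ρ = 0.5, rank-sum has 43% power where signed-rank has 73%; the gap is smaller at ρ = 0.3 and larger at ρ = 0.7. These sizes depend on an assumed effect and correlation that the documents do not give, and they apply only if the unpaired tests are in fact run on the weekly samples. The loss of power held at every correlation tried.

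**What to change.** - **Pre/post rule:** replace the fused Friedman and rank-sum phrase by signed-rank for two weeks and Friedman for more than two.
- **Alpha diversity and log-transformed calprotectin and lipocalin-2:** state that ANOVA is repeated-measures, or use a linear mixed model with cracker type as fixed effect and a participant random intercept. Leave out a categorical week term, for the reason in step 4 of the working; include at most a linear week trend.
- **Beta diversity between time points:** restrict adonis and PERMDISP permutations within participant, and say so.
- **Operational taxonomic units between weeks:** instead of Metastats, use the mixed models already listed, with participant as random effect, or paired tests.
- **Leave unchanged:** the rank-sum tests between response groups in Response Analysis, which compare different people.

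The cost is a few sentences and a few lines of code. The samples and the data stay the same.

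### The Friedman and repeated-measures ANOVA options use only participants with all four samples, although the protocol foresees cracker-related dropout; a mixed model would keep the partial data at almost no cost

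*Protocol article*

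**What the plan says.** The protocol article "will enroll 30 adults" (Setting and Participant Recruitment). Under Design, "A total of 4 stool samples will be collected from each participant over the course of the study", one at the end of each week: A and C on refined crackers, B and D on whole-wheat crackers. Under Outcomes, "The primary outcome measure will be the alpha diversity of the gut microbiota".

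The tests named for repeated samples are:

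- **Alpha diversity** (Statistical Analyses): "ANOVA and Wilcoxon signed-rank test or Friedman test with post hoc comparisons will be used to compare alpha diversity across treatment categories after intervention".
- **Butyrate genes** (Butyrate Gene Analyses): "A one-way repeated-measures analysis of variance (ANOVA) will be performed on each set of data".
- **Genera and phyla above 1% abundance** (Statistical Analyses): changes "will be determined across time points using the Friedman test with post hoc comparisons". Friedman is also named within enterotypes.
- **Mixed models** (Statistical Analyses), for taxa only: "Where appropriate, the negative binomial and zero-inflated mixed models in the R package will be used to test for differences in taxa abundance over time".
- **Butyrate capacity and inflammation markers** (Abstract, Results): parametric methods, with ANOVA and linear regression as examples.

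On dropout, Strengths and Weaknesses calls retention a potential limitation, suggests that participants may grow tired of the crackers' taste, and concludes: "A high dropout rate could hinder our ability to detect statistically significant differences". It gives no dropout rate.

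**The concern.** The Friedman test ranks the four values within each participant, and classical one-way repeated-measures ANOVA works on a full participant-by-week table. A participant who stops after week 3 has given A, B and C, including a refined and whole-wheat pair, but cannot enter either test. That person must be dropped, have the missing value filled in, or be analysed by another method.

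Two things are at stake. The first is efficiency: samples already collected on the primary outcome go unused in these tests, in a study of 30. The second is what the result describes. The only cause of dropout that the protocol suggests is the study food, so those who finish may differ from those who leave. The protocol mentions only the loss of power. It names mixed models, which tolerate missing weeks, for taxa abundance but not for alpha diversity, butyrate genes or inflammation markers.

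**Working it through.** **Inputs from the protocol.** 30 participants and 4 samples each, so 30 × 4 = 120 if complete. The article gives no power calculation, standard deviation or dropout rate, so there is no stated figure to reproduce. Every dropout rate and correlation below is an assumption.

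**1. Do the tests need complete blocks?** A Friedman test run on a 30 × 4 table with one empty cell returns no statistic. The participant has to be removed or the value imputed.

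**2. Samples lost under steady dropout** (leavers spread evenly after weeks 1, 2 and 3).

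| Assumed dropout | Participants by week | Collected | In complete blocks | Unused |
|---|---|---|---|---|
| 10% | 30/29/28/27 | 114 | 27 × 4 = 108 | 6 (5%) |
| 20% | 30/28/26/24 | 108 | 24 × 4 = 96 | 12 (11%) |
| 30% | 30/27/24/21 | 102 | 21 × 4 = 84 | 18 (18%) |

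If samples are instead missing sporadically, 5% per sample leaves 30 × 0.95⁴ = 24.4 complete blocks, against 30 × 0.95² = 27.1 for any single pair of weeks. At 10% the figures are 30 × 0.90⁴ = 19.7 and 30 × 0.90² = 24.3.

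**3. Variance, complete cases against all samples.** Assume total variance 1 and equal correlation ρ between any two weeks of one person. With n complete participants:

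- whole wheat minus refined, (B+D)/2 − (A+C)/2: variance (1−ρ)/n
- B − A: variance 2(1−ρ)/n

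With all samples, the variance of a contrast c is c′(Σ Xᵢ′Vᵢ⁻¹Xᵢ)⁻¹c, where Vᵢ covers only the weeks that person provided. A paired B − A comparison of everyone with both weeks has variance 2(1−ρ)/n_B, with n_B = 28 or 27.

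| Pattern, ρ | Contrast | Complete cases | All samples | Ratio | Available pairs ÷ all samples |
|---|---|---|---|---|---|
| 30/28/26/24, 0.5 | whole − refined | 0.5/24 = 0.0208 | 0.0189 | 1.10 | – |
| 30/28/26/24, 0.8 | whole − refined | 0.2/24 = 0.0083 | 0.0076 | 1.10 | – |
| 30/27/24/21, 0.5 | whole − refined | 0.5/21 = 0.0238 | 0.0204 | 1.17 | – |
| 30/27/24/21, 0.8 | whole − refined | 0.2/21 = 0.0095 | 0.0082 | 1.16 | – |
| 30/28/26/24, 0.5 | B − A | 1/24 = 0.0417 | 0.0351 | 1.19 | (1/28)/0.0351 = 1.017 |
| 30/28/26/24, 0.8 | B − A | 0.4/24 = 0.0167 | 0.0142 | 1.17 | (0.4/28)/0.0142 = 1.007 |
| 30/27/24/21, 0.5 | B − A | 1/21 = 0.0476 | 0.0361 | 1.32 | (1/27)/0.0361 = 1.026 |
| 30/27/24/21, 0.8 | B − A | 0.4/21 = 0.0190 | 0.0147 | 1.30 | (0.4/27)/0.0147 = 1.010 |

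The last column matters. For B − A, the complete-block penalty of 17-32% shrinks to about 1-3% if the comparison simply uses everyone with both weeks.

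**4. Power of the four-week test.** Simulation, 2000 runs per scenario, assuming ρ = 0.6, an effect of 0.45 SD at B and D, two-sided 0.05, and dropout unrelated to outcome.

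| Assumed dropout | Friedman, complete | Repeated-measures ANOVA, complete | Linear model (participant + week), all samples |
|---|---|---|---|
| 0% | 0.80 | 0.91 | 0.90 |
| 10% | 0.76 | 0.86 | 0.88 |
| 20% | 0.72 | 0.82 | 0.86 |
| 30% | 0.62 | 0.77 | 0.83 |

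Most of the gap between the first and last columns comes from ranks against a parametric test on normal data. The like-for-like gain from keeping partial data is the last column minus the middle one: about 2, 4 and 6 points at 10, 20 and 30%. With no dropout those two tests are the same, so the 1-point difference in the first row shows the simulation error. These runs do not measure selection, because dropout was simulated as unrelated to outcome.

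**The case against.** Four points on the other side carry weight.

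- **Partial data are usable elsewhere in the plan.** A reader might infer that one missing week removes a participant altogether. The documents do not support that. The sentence on alpha diversity also names the signed-rank test, which needs only the two weeks compared, and an ANOVA whose form is not fixed. The Abstract allows linear regression for butyrate capacity and inflammation markers. PERMANOVA and the taxa mixed models do not require all four samples. This stands, and it confines the point to the Friedman and repeated-measures ANOVA options. It does not remove it: signed-rank is pairwise, and an ANOVA that ignored pairing would give up the within-person comparison that the protocol counts as a strength.
- **Dropout is possible, not forecast.** A reader might infer that the protocol expects it. Strengths and Weaknesses words it as something that may happen, with no rate. This stands.
- **No complete-case rule is written.** Missing-data handling is commonly left to a fuller document, and its absence here is no fault. This stands too. The point rests on the tests that are named, which cannot take an incomplete participant as they are.
- **Selection bias is not shown.** A reader might infer that completers' results are biased, for instance because symptoms after a whole-wheat week drive people out. The protocol mentions only tiring of the taste, crackers are eaten in all four weeks, and nothing links that to change in diversity. Selection is possible but unquantified.

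**Conclusion.** The point holds in limited form. The protocol foresees dropout linked to the study food, yet the four-week tests it names for alpha diversity (as one option), butyrate genes and taxa use only participants with every sample. No method named for the primary outcome clearly keeps partial data across all four weeks while respecting the pairing.

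The cost is modest. Under the two heavier assumed patterns (20% and 30% dropout, ρ 0.5 to 0.8), complete-case variance for whole wheat minus refined is about 10% or 16-17% higher than with all samples. The protocol does not itself define that pooled contrast as a test. For a single pair such as B − A, available-pair testing already recovers nearly all of the loss. The power gain of about 2 to 6 points rests on an assumed 10-30% dropout. Any reduction in selection bias holds only if data are missing at random given the observed values. The change is worth making because it is nearly free and the protocol already uses mixed models for taxa.

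**What to change.** For alpha diversity, log gene copies, calprotectin and lipocalin-2 (transformed if skewed):

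1. Make the main analysis a linear mixed model with time point/cracker as fixed effect and participant as random intercept, fitted to every sample provided, including those from participants who later leave.
2. Keep the Friedman test on complete participants as a sensitivity analysis.
3. State that the model's validity rests on missingness at random given the observed data.
4. Describe the early-week values of leavers beside those of stayers. This indicates the risk of selection but cannot exclude it.
5. Extend the sentence on dropout in Strengths and Weaknesses to say that complete-block results describe completers.

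The cost is revised analysis wording and a few lines of R, with no extra samples or participants. The downside is a model-based normality assumption, to be checked on residuals, and slightly more analysis work.
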